### Study interventions

2.3

#### Treatment group

2.3.1

Treatment group Patients will oral Yuanhu Zhitong dropping pills, 10 pills, 3 times a day. The treatment period will last 4 weeks. Drugs are provided by Gansu Longshen Rongfa Pharmaceutical Company. The approval is No. Z20010024.

#### Control group

2.3.2

Control group Patients will oral diclofenac sodium sustained-release capsules 100 mg once per day, drugs are provided by Xiansheng Pharmaceutical Company. The treatment period will also 4 weeks. The approval is H20023856.

### Sample size calculation

2.4

Preliminary estimates put the number of cases in each group at 25. Considering the influence of shedding and elimination (20%), the overall sample size was set as 60 cases, 30 cases in the experimental group and 30 cases in the control group.

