## Introduction

1

Knee osteoarthritis (KOA) is a common chronic knee disease, with pain and limited function as the main causes.^[1,2]^ More than 9,000,000 people have been diagnosed with KOA through clinical and imaging methods in USA.^[3]^ In China, 19.4% of the elderly population more than 60 years of age suffer from KOA.^[4,5]^ According to the Bulletin of the World Health Organization, osteoarthritis is predicted to be the fourth leading cause of disability by 2020.^[6]^ Patients often have symptoms such as pain and dysactivity, which limits the mobility of patients, cause psychosocial problems such as low self-efficacy and depression, and decreases the quality of life.^[7,8]^ The current therapeutic for KOA were mainly aimed to reducing pain and improvement of joint mobility.^[9,10]^

According to the recent guidelines, knee replacement surgery was the only effective pain management approach for the end-stage KOA.^[11,12]^ For the non-surgical treatment of KOA, pharmacological, non-pharmacological and alternative treatments were widely applied in the clinical practice.^[13]^ Among them pharmacologic treatments were the mostly widely adopted. For example acetaminophen, topical treatment, nonsteroidal, anti-inflammatory drugs (NSAIDs), COX-2 inhibitors, opioids and intra-articular cartilage-protective agents.^[14]^ However, long time taking anti-inflammatory drugs was associated with serious adverse reactions, such as digestive and renal impairment.^[15]^ A number of patients had to stop taking drugs for the side effects. Most patients are unwilling to receive routine treatment due to side effects, contraindications, and unsatisfactory relief of symptoms.^[16]^ while not all the patients are the ideal surgical candidates, some patients afraid of operation. Therefore non-invasive, safe and effective treatment options are in great demand for those patients to improve symptoms.

Chinese medicine has been used to manage osteoarthropathy for thousands of years. Yuanhu Zhitong dropping pills were also applied for treat KOA. However its efficacy and security has not been reported in the literature. The purpose of this study is to assess the efficacy and security of Yuanhu Zhitong dropping pills for KOA, a large sample size and a reliable blind method will be used to draw a reliable conclusion.

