### Randomization and allocation concealment

2.5

Sixty patients will be divided into Yuanhu Zhitong dropping pills and Diclofenac Sodium Sustained Release Capsules groups with a ratio of 1:1, random number table will be used for divide the groups. Only the chief orthopedic physicians will be allowed to know the differences of the groups.

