## Discussion

4

The results showed that the Yuanhu Zhitong Drop Pill group was superior to the Western medicine group in terms of VAS scores, WOMAC scale assessment results, patient satisfaction, and gastrointestinal symptoms assessment scale (GSRS scale),^[22]^*P* < .05, adverse reactions. The number of cases was significantly less than that of the western medicine group. This shows that Yuanhu Zhitong drop pills can effectively relieve limb pain without side effects, can improve the quality of life of patients, and has a significant effect.

In recent years, with the continuous development of traditional Chinese medicine research, it has achieved significant results in the treatment of knee osteoarthritis. At the same time, with its unique advantages such as multiple targets for therapeutic effects and low toxic and side effects, it has obtained a large number of patients and doctors. There are still many deficiencies in the research of traditional Chinese medicine for knee osteoarthritis. There are some limitations with this study. First, the sample size of this study is small and it is a single-center randomized controlled study. Second, patients using VAS scores are too subjective. Third, a large number of clinical studies lack long-term efficacy. The safety of the drug need long time to observe.

Therefore, large-scale randomized double-blind controlled experiments should be carried out in future clinical research to strive for innovative and prospective related studies with rich center points and large sample sizes. In conclusion, we hope that the results of this study can provide new evidence for the treatment of early knee osteoarthritis pain with traditional Chinese medicine.

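### The 20% loss allowance in section 2.4 is applied as a mark-up: 30 per group less 20% leaves 24, one short of the 25 stated as needed

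*Protocol article*

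**What the plan says.** Section 2.4 (Sample size calculation) of the protocol article takes three steps.

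- The requirement: "Preliminary estimates put the number of cases in each group at 25".
- The allowance and the total: "Considering the influence of shedding and elimination (20%), the overall sample size was set as 60 cases".
- The split: "30 cases in the experimental group and 30 cases in the control group".

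Section 2.5 (Randomization and allocation concealment) repeats sixty patients, allocated "with a ratio of 1:1, random number table will be used for divide the groups". The article gives no other loss rate and no other evaluable target.

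**The concern.** A sample size section should let the reader go from the number enrolled, through the expected loss, back to the number needed for analysis. Here that check fails. The 20% is tied to drop-out and elimination, which are losses from the enrolled patients, but the arithmetic adds 20% to the evaluable target instead. The size so obtained misses its own target at its own loss rate. What is at stake is the accuracy of the statement and a small amount of precision. The validity of the comparison is not affected.

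**Working it through.** **Inputs, all from section 2.4:** evaluable requirement n = 25 per group; loss d = 20%; planned enrolment 30 per group, 60 in total. The 1:1 ratio is in section 2.5.

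**1. Reproduce the plan's figure.** n × (1 + d) = 25 × 1.20 = 30 per group, 60 in total. This matches exactly and shows how the allowance was applied.

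**2. Apply the stated loss to the stated enrolment.** 30 × (1 − 0.20) = 24 per group, or 48 of 60. The target is 25 per group, or 50. The shortfall is 1 per group, 2 in total.

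**3. Loss that 30 per group can absorb.** 1 − 25/30 = 0.167, or 16.7%.

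**4. Enrolment that would meet the target at 20% loss.** n / (1 − d) = 25 / 0.80 = 31.25, rounded up to 32 per group, 64 in total. Check: 32 × 0.80 = 25.6, which is at least 25. (Inflating only the total gives 50 / 0.80 = 62.5, so 63, but equal groups need 64.)

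**5. What one patient per group costs in power.** The article states no power, so assume that 25 per group was sized for 80% or 90% power in a two-sided comparison of two independent means. With the normal approximation, the implied standardised difference is δ = (z₁₋α/₂ + z_power) × √(2/25), and the power at 24 per group is Φ(δ × √(24/2) − z₁₋α/₂).

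| Two-sided α | Assumed power at 25 | δ (SD units) | Power at 24 | Loss (points) |
|---|---|---|---|---|
| .05 | 80% | 0.792 | 78.4% | 1.6 |
| .05 | 90% | 0.917 | 88.8% | 1.2 |
| .01 | 80% | 0.967 | 78.0% | 2.0 |
| .01 | 90% | 1.091 | 88.6% | 1.4 |

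Both levels are shown because section 2.4 names none; section 2.11 uses .01 as its threshold for significance.

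**6. The same cost as a detectable difference.** For a two-sample t test at 80% power, going from 25 to 24 per group moves the detectable difference from 0.809 to 0.826 SD at .05 (0.826 − 0.809 = 0.017 SD) and from 1.001 to 1.024 SD at .01 (1.024 − 1.001 = 0.023 SD). These are slightly larger than the δ values in step 5 because they use the t distribution.

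**The case against.** **The 20% may be a mark-up.** On that reading 25 × 1.2 = 30 is exact and nothing is miscalculated. This is possible, but the percentage is attached to drop-out and elimination, which reads more naturally as a loss rate. Even as a mark-up, a reader would take it as protection against a 20% loss, and it protects only against 16.7%. The sentence needs correcting on either reading.

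**The effect is negligible.** Multiplying by 1.2 is a common shortcut, and no decision in the trial turns on one patient per group. This stands, and it sets the weight of the point.

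Some stronger readings are tempting, but the documents do not support them as part of this point.

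- *That the slip leaves the trial able to detect only a very large difference.* The detectable difference of 0.826 SD at .05, or 1.024 SD at .01, belongs to any trial of about 25 per group. With 32 enrolled and 25.6 evaluable it would still be about 0.80 and 0.99 SD. Converting these values to millimetres needs an SD, which the article does not give. They also presume a between-group t test, whereas section 2.11 names a non-parametric or paired test.
- *That the 25 has no basis.* The article calls it a preliminary estimate and gives no difference, SD, significance level or power for it. A journal article may leave these to the full protocol, which is not shown, so their absence is not a finding here.
- *That the article's own descriptions of its size confirm the error.* The Introduction promises "a large sample size and a reliable blind method will be used to draw a reliable conclusion", while the Discussion concedes that "the sample size of this study is small". The two descriptions conflict, but neither bears on the 20% calculation.
- *That the analysis set should be changed as the remedy.* Which patients are analysed is a separate matter. A requirement to analyse all 30 per group would also sit badly beside a statement based on 24.

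**Conclusion.** The point holds as a minor arithmetic correction. As written, 30 per group does not yield 25 evaluable at a 20% loss: it yields 24. The size is one evaluable patient per group, two in total. The shortfall itself rests only on the figures in section 2.4, with the 20% read as a loss rate among enrolled patients. The cost of 1.2 to 2.0 percentage points of power rests on the further assumptions that 25 was sized for 80% to 90% power and that two independent means are compared. Nothing here shows that the trial is materially underpowered or that its size must change.

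**What to change.** Keep 60 patients and restate section 2.4 along these lines: *30 per group allows for a loss of 16.7% (25 evaluable per group); at a 20% loss 24 per group remain.*

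This costs one sentence and no patients. If the sponsor prefers to keep both the 25 and the 20% as stated, enrolment would be 32 per group, 64 in total, which is four more patients. Given how little power is at stake, the restatement is enough.

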### Randomization and allocation concealment

2.5

Sixty patients will be divided into Yuanhu Zhitong dropping pills and Diclofenac Sodium Sustained Release Capsules groups with a ratio of 1:1, random number table will be used for divide the groups. Only the chief orthopedic physicians will be allowed to know the differences of the groups.

### Single-blinding

2.6

Treatment and Control practitioners were not provided details of treatment plans or grouping information within the envelope in advance. No participant or relevant medical personnel was authorized to interfere with individual treatment selections. Evaluators are blinded to the treatment each patient has received, their function being to assist each patient in completion of the various questionnaires and scoring the respective scales. It is intended that the independent biostatisticians are also blinded when conducting the statistical analysis.

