### Study design

2.1

This study will be a single-blinded, randomized, and Diclofenac Sodium Sustained Release Capsules controlled trial. It will be performed at Gansu Provincial Hospital of Traditional Chinese Medicine, Lanzhou, China. The project was evaluated and approved by the Research Ethics Committee of Gansu Provincial Hospital of Traditional Chinese Medicine (Ethical batch No. FJ/04-IRB/C/018-V3.0, Ethics Review Adoption Form places in the Supplemental Digital Content). We planned to begin recruiting patients from July 2019, Patients with stage I, II, and III knee osteoarthritis will be recruited. In this study, there will be 8 investigators. Including 1 chief orthopedic physician, 5 orthopedic physicians, 2 outcome assessors. Five orthopedic physicians will recruit patients. The included patients should meet the inclusion criteria and will introduce the patient to the trial process. The 5 orthopedic physicians will also tell the participants possible benefits and risks.

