#### Primary outcomes pain^[18,19]^

2.8.1

When the patient takes the medicine, it will be recorded as the first day. Patients will mark on a 100 mm visual analogue scale to assess the pain of their knee (from no pain to severe). At the end of 1, 2, 3, and 4 week, patients themselves and the assessors will record it.

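### The promise of reliable blinding is not supported for the primary outcome: patients can very likely recognise their arm, and they rate the pain scale themselves

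*Protocol article*

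**What the plan says.** All references are to the protocol article.

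- **The claim.** The Introduction ends: "a large sample size and a reliable blind method will be used to draw a reliable conclusion". Section 2.1 adds: "This study will be a single-blinded, randomized, and Diclofenac Sodium Sustained Release Capsules controlled trial".
- **The regimens.** Section 2.3.1: "Treatment group Patients will oral Yuanhu Zhitong dropping pills, 10 pills, 3 times a day". Section 2.3.2: "Control group Patients will oral diclofenac sodium sustained-release capsules 100 mg once per day". Both run for 4 weeks. Neither section mentions a dummy, matched appearance or masked packaging.
- **Who is blinded.** Section 2.6: "Evaluators are blinded to the treatment each patient has received, their function being to assist each patient in completion of the various questionnaires". The evaluators also score the scales. The biostatisticians are intended to be blinded. Practitioners are only kept uninformed beforehand, which is allocation concealment and not blinding during treatment. Patients are not named as blinded.
- **Who may know the groups.** Section 2.5: "Only the chief orthopedic physicians will be allowed to know the differences of the groups".
- **Who rates the outcomes.** Section 2.8.1, on the primary outcome: "Patients will mark on a 100 mm visual analogue scale to assess the pain of their knee". At the end of weeks 1 to 4, "patients themselves and the assessors will record it". Section 2.8.2.1 has WOMAC recorded in the same way and has patients fill in the satisfaction questionnaire themselves.

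**The concern.** Blinding protects an outcome only if the person who produces the value is blinded. Here the pain score comes from the patient, while the blinding covers those who help with, score and analyse the forms. A patient who knows which drug is being taken may report pain in line with what is expected of a traditional medicine or of a standard NSAID. Blinding the evaluator or the statistician cannot remove a bias that enters with the patient's own mark. The same applies to satisfaction, and to WOMAC so far as it is the patient's report.

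A second route runs through the evaluator. Someone who sits with an unblinded patient to complete forms can easily be told the treatment, which would weaken the one layer of blinding that the design does have.

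What is at stake is the weight of the efficacy conclusion. The Introduction rests the reliability of that conclusion partly on the blinding.

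**Working it through.** **1. The statements side by side**

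| Question | What the article gives | Section |
|---|---|---|
| Do the arms look alike to the patient? | Dropping pills, 10 × 3 = 30 a day, against a once-daily sustained-release capsule dose: different form, count and schedule | 2.3.1, 2.3.2 |
| Is a means of masking patients described? | None | 2.3, 2.6 |
| Who is blinded? | Evaluators; biostatisticians by intention | 2.6 |
| Who produces the primary outcome? | The patient | 2.8.1 |
| What does the blinded evaluator do? | Helps with questionnaires and scores scales | 2.6 |
| Who may know the groups? | Only the chief orthopedic physicians | 2.5 |

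Rows 1 and 2 make it very likely that patients recognise their arm. Rows 3 to 5 show that the blinded parties do not generate the primary outcome. The last row, read literally, does not fit row 1.

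**2. How much a reporting shift could matter (illustration only)**

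The article gives no figure of its own to reproduce on this point.

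Inputs from the article: 25 patients per group (section 2.4, before the allowance for losses) and a significance threshold of .01 (section 2.11).

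Assumed inputs, because the article gives none: SD of the VAS of 12, 20 or 30 mm; a difference between arms of 5 or 10 mm that arises from reporting alone; no true drug difference; a two-sided t-test comparing the two independent arms.

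Formulas: SE = SD × √(2/n). Noncentrality = shift / SE. The false-positive rate is the probability that a noncentral t with 2n − 2 = 48 degrees of freedom exceeds the critical value 2.682 in absolute value.

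For SD 20 mm: SE = 20 × √(2/25) = 5.66 mm. A 5 mm shift gives noncentrality 5/5.66 = 0.88 and a rate of 0.043. A 10 mm shift gives 1.77 and a rate of 0.193.

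| Assumed SD | SE | 5 mm shift | 10 mm shift |
|---|---|---|---|
| 12 mm | 3.39 mm | 12.5% | 60.6% |
| 20 mm | 5.66 mm | 4.3% | 19.3% |
| 30 mm | 8.49 mm | 2.3% | 7.5% |

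The nominal rate is 1%. With 30 per group and SD 20 mm, the rates are 5.1% and 24.4%. The spread shows that the figures depend mainly on the assumed inputs.

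**The case against.** - **Single-blind is not a false label.** Evaluator-blind is an ordinary meaning of the term, and section 2.6 says who is blinded. This stands. A reader might infer that the article misreports its design by calling itself single-blinded; the text does not support that. What remains is the reliability claim in the Introduction.
- **The absence of dummies is read from silence.** This is a condensed article, and packaging or dummy supply may be set out in a full protocol. This stands in part. A reader might infer as fact that every patient knows the treatment and that the trial is simply open-label. The article does not say what patients are told or how the drugs are labelled. But it has sections for both regimens and for blinding, and neither mentions patient masking, so recognition is very likely on the text as given.
- **Section 2.5 may concern staff access to the allocation.** It stands under allocation concealment and can be read that way. A reader might infer that the sentence cannot be true; it is unclear rather than proven wrong.
- **Evaluator help is limited.** Patients mark the VAS and complete the satisfaction form themselves, so evaluator unblinding is a risk and not something the article shows. Section 2.6 nevertheless gives evaluators the task of helping with the questionnaires.
- **The Discussion is candid.** It calls patient VAS scores too subjective and asks for double-blind trials in future. It does not say that patients here are unblinded, and the claim in the Introduction stays uncorrected.
- **Bias may go either way.** Expectation could favour the established NSAID as well as the traditional medicine. This stands, and no direction is claimed.

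**Conclusion.** The point holds in a limited form. The article claims a reliable blind method, and the design as described does not have that property for its primary outcome: the regimens differ visibly, no patient masking is described, and the patient marks the VAS. The conclusion assumes that no undisclosed masking exists.

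The size and direction of any bias cannot be derived from the documents. Under the stated assumptions, the false-positive rate at the .01 threshold is about 2% to 12% for a 5 mm shift and about 8% to 61% for a 10 mm shift. These figures show only that a modest shift could matter with 25 per arm; they are not an estimate for this trial. Using different regimens without a dummy is a design choice and not in itself an error. The fault lies in the claim made for the blinding and in the handling of the forms.

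**What to change.** 1. In sections 2.1 and 2.6, describe the trial as evaluator- and analyst-blinded with patients not blinded. If a dummy or other masking exists, state it instead.
2. Delete the reliable-blinding claim from the Introduction.
3. Reconcile the sentence in section 2.5 on who may know the groups with sections 2.3.1, 2.3.2 and 2.6, for example by saying whether it refers to staff access to the allocation.
4. Have patients complete the VAS and WOMAC alone before meeting the evaluator, with an instruction not to reveal their treatment. Limit the evaluator to checking completeness and scoring.
5. State with the efficacy conclusions that they rest on self-report by patients who are not blinded.

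The cost is a less favourable description of the trial and a small change in how the forms are handled. A double dummy would address the cause but needs placebo supply; it is an option, not a condition of this correction.

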### Discontinuation criteria

2.7

1.Occurrence of anaphylaxis or severe adverse events;2.It was found in the study that the therapeutic effect was too poor to have clinical value;3.It is difficult to evaluate the curative effect because of the important deviation in the design or implementation of the clinical research scheme.

### Outcomes

2.8

#### Primary outcomes pain^[18,19]^

2.8.1

When the patient takes the medicine, it will be recorded as the first day. Patients will mark on a 100 mm visual analogue scale to assess the pain of their knee (from no pain to severe). At the end of 1, 2, 3, and 4 week, patients themselves and the assessors will record it.

#### Secondary outcomes

2.8.2

##### Knee function and patient satisfaction

2.8.2.1

Knee function will be measured The Western Ontario and McMaster Universities Osteoarthritis Index (WOMAC),^[20,21]^ patients themselves and the assessors will also record it at the end of 1, 2, 3, and 4 week. We will record the patient satisfaction at the time their treatment period is finished. A questionnaire will be applied. The questionnaire will be divided into 4 stages, including very satisfied, satisfied, just like, and not satisfied. Patients will fill in the questionnaire by themselves.

### Complications and adverse events during and after treatment

2.9

All expected and unexpected adverse events will be recorded during practitioner contact time throughout the study. The adverse events associated with both drugs are usually the possible occurrence of the immune system during treatment (rash, macular rash, urticaria, allergic reaction); Central system (dizziness); Digestive system (nausea, vomiting, diarrhea or abdominal discomfort); Respiratory system (difficulty breathing); Cardiovascular system (chest tightness, palpitations, shortness of breath); Others (dry mouth, fever, chills). All serious adverse events will be reported immediately to the study contact for further investigation of the cause.

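### Adverse events are tied to contact with practitioners whose blinding is unsettled, while the weekly blinded assessors have no stated adverse-event role, so the safety comparison is open to differential ascertainment

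*Protocol article*

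**What the plan says.** The Introduction gives the purpose as assessing both efficacy and safety (the article's word is security). The Discussion draws a between-arm safety conclusion, with fewer adverse-reaction cases on the test drug than on the comparator.

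On capture, section 2.9 (Complications and adverse events) says "All expected and unexpected adverse events will be recorded during practitioner contact time throughout the study". It then lists the body systems in which events usually occur. It describes no common question, schedule or blinded recorder.

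On blinding:
- Section 2.1 (Study design): "This study will be a single-blinded, randomized, and Diclofenac Sodium Sustained Release Capsules controlled trial".
- Section 2.5 (Randomization and allocation concealment): "Only the chief orthopedic physicians will be allowed to know the differences of the groups".
- Section 2.6 (Single-blinding), on the practitioners: "Treatment and Control practitioners were not provided details of treatment plans or grouping information within the envelope in advance".
- Section 2.6, on the evaluators: "Evaluators are blinded to the treatment each patient has received, their function being to assist each patient in completion of the various questionnaires". The statisticians are also meant to be blinded.

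On contacts, section 2.8.1 says of the pain score: "At the end of 1, 2, 3, and 4 week, patients themselves and the assessors will record it". Section 2.8.2.1 sets the same four time points for WOMAC.

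On treatment, sections 2.3.1 and 2.3.2 give 10 pills three times a day in one arm and a once-daily capsule regimen in the other. No dummy is described.

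**The concern.** A comparison of adverse-event counts is fair only if events are looked for equally hard in both arms. When recording depends on what comes up in contact with a practitioner, the count depends on how often the two meet, what is asked, and what the practitioner expects to hear. If the practitioner knows or can guess the drug, those things can differ by arm.

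The setting invites such expectations. The Introduction justifies the trial by the harms of the comparator's drug class: "long time taking anti-inflammatory drugs was associated with serious adverse reactions, such as digestive and renal impairment". The Discussion describes the test drug as free of side effects. A safety advantage is therefore a headline claim, and unequal questioning could create it, inflate it or hide it.

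The design already has a more even-handed contact. Assessors record outcomes for every patient in both arms on the same four occasions, and the evaluators are blinded. The article gives them no part in collecting harms.

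**Working it through.** The article states no adverse-event figure, so there is nothing to reproduce. The check sets the sections side by side and then illustrates on assumed rates.

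**1. Who records.** Section 2.9 names practitioners. The evaluators' function in 2.6 covers questionnaires and scales, not adverse events. (I take the evaluators of 2.6 to be the two outcome assessors of 2.1.)

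**2. What the recorders know.** Section 2.6 says the practitioners lacked the grouping information beforehand. It does not say they stay blind afterwards, and it refers to them by arm. Section 2.5, read literally, keeps the groups from everyone except the chief orthopedic physicians. These statements do not settle whether a practitioner is blind during the four weeks of treatment.

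**3. Whether blinding could be kept.** The regimens differ in dosage form and daily frequency. Anyone who hands out or discusses the drug can tell them apart, and so can the patient.

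**4. How large the effect could be.** From the article: 30 patients per arm (section 2.4). Assumed, because the article gives no rates: the same true risk *t* of an adverse event in both arms, with a share *a* = 90% of affected patients recorded in one arm and *b* = 70% or 50% in the other.

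Recorded risks are p₁ = *ta* and p₂ = *tb*. The spurious difference is d = *t*(*a* − *b*) and the spurious ratio is *b*/*a*. The chance of two-sided p < 0.05 in that direction is approximately Φ[(d − 1.96·se₀)/se₁], where p̄ = (p₁ + p₂)/2, se₀ = √(p̄(1 − p̄)·2/30) and se₁ = √((p₁(1 − p₁) + p₂(1 − p₂))/30).

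| True risk, both arms | Capture | Recorded risk | Difference (points) | Ratio | Chance of p < 0.05 |
|---|---|---|---|---|---|
| 20% | 90% v 70% | 18% v 14% | 4 | 0.78 | 6.2% |
| 20% | 90% v 50% | 18% v 10% | 8 | 0.56 | 14.1% |
| 30% | 90% v 70% | 27% v 21% | 6 | 0.78 | 7.8% |
| 30% | 90% v 50% | 27% v 15% | 12 | 0.56 | 20.4% |
| 40% | 90% v 70% | 36% v 28% | 8 | 0.78 | 9.7% |
| 40% | 90% v 50% | 36% v 20% | 16 | 0.56 | 27.8% |

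Worked last row: p̄ = 0.28, se₀ = √(0.28 × 0.72 × 2/30) = 0.1159, se₁ = √((0.2304 + 0.16)/30) = 0.1141. Then (0.16 − 1.96 × 0.1159)/0.1141 = −0.589, and Φ(−0.589) = 0.278.

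With equal capture the chance in one direction is 2.5%. At the article's own threshold of P < .01 (section 2.11), 1.96 becomes 2.576. The last row is then Φ[(0.16 − 0.2986)/0.1141] = Φ(−1.215) = 11%, against 0.5% with equal capture. This is a normal approximation with few events; an exact test would reject less often.

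**The case against.** The strongest reply is that a condensed article commonly leaves the wording of questions, the visit forms and the recorder to the full protocol, so their absence is no fault. This stands for detail that is merely missing. It does not cover the route that the article does state, or the unsettled blinding between 2.5 and 2.6.

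A reader might infer several stronger things that the text does not support:
- *Practitioners know the arm.* Section 2.5 points the other way, and the sentence in 2.6 can be read as being about allocation concealment. Unblinded practitioners are plausible but not stated.
- *Events come only through treating practitioners, with different people in each arm.* Section 2.9 excludes no other route. Section 2.1 lists five orthopedic physicians and assigns none to an arm. Section 2.10 mentions two research assistants who collect data.
- *The comparison is biased, and in favour of the test drug.* Neither direction nor size can be shown. Even a halved count of 6 v 3 out of 30 (20% true risk, with full capture against half) gives a Fisher p of 0.47.
- *Renal harm is missed.* The list in 2.9 has no renal item, but unexpected events are recorded too, and the Introduction links renal harm to long use, whereas treatment here lasts 4 weeks.

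The Discussion also names a gastrointestinal symptom scale. If the evaluators administer it, some harms would be captured under blinding. It appears in neither 2.8 nor 2.9, so this cannot be relied on.

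Finally, blinded questioning cannot stop patients who recognise their drug from reporting differently. That is correct, and it limits what any fix can achieve.

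**Conclusion.** The concern holds as a risk of differential ascertainment, not as a demonstrated bias. Three facts support it: the stated recording route runs through practitioners whose blinding sections 2.5 and 2.6 leave unsettled; the regimens can be told apart; and the blinded weekly assessors have no stated adverse-event role. It matters because safety is a stated aim and the arms are compared on it.

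The size is unknown. The illustration gives a spurious difference of 4 to 16 points and a 6% to 28% chance of p < 0.05 in that direction, against 2.5% with equal capture. All of this rests on assumed risks of 20% to 40% and assumed capture of 90% against 50% to 70%. With other capture rates the effect could be nil or reversed. The change is worth making because it is cheap and a headline claim depends on the comparison.

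**What to change.** - Reconcile sections 2.5 and 2.6, and state for each role (patient, practitioner, evaluator, research assistant, statistician) whether it is blinded and until when.
- At the end of weeks 1, 2, 3 and 4, **after** VAS and WOMAC are completed, give every patient in both arms the same fixed checklist: the items already in section 2.9 plus an open question on anything else. Self-completion is preferable; otherwise the blinded evaluator reads it out.
- Base the between-arm adverse-event comparison on this checklist. List events volunteered to practitioners separately.

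The order matters. Asking about harms first could prime patients just before a subjective pain rating, and could hint at the arm to the person helping to record the primary outcome.

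The cost is a short form and a few minutes at four existing assessment points. Solicited questions will raise the recorded event rate in both arms. Symptoms reported at one visit may still hint at the arm to the evaluator at later visits; self-completion reduces this. The change does not cure reporting bias in patients who recognise their drug.
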